#### Secondary implementation outcomes

Secondary implementation outcomes are measures of adoption, dose delivered, reach, fidelity and sustainability. These are measured both with respect to the delivery of brief physical activity counselling within routine physiotherapy care and delivery of the multi-faceted implementation strategy to support and train physiotherapists. These five measures are recommended as essential outcome measures in evaluating implementation studies [52]. See Table 3 for how each measure is being operationalised in this trial.

**Table 3 Tab3:** List of implementation outcome measures included as part of the BEHAVIOUR study

Implementation outcomes	Delivery of physical activity counselling		Delivery of multi-faceted implementation strategy	
	Definition of outcome	Measurement tool	Definition of outcome	Measurement tool
Reach	Reach of the delivery of physical activity counselling will be measured in three ways: (1) Proportion of eligible new physiotherapy patients who receive physical activity counselling^a^; (2) Percentage of patient participants that are from culturally and linguistically diverse backgrounds; (3) Percentage of community physical activity providers referred to from number identified within the study.	1. Study screening log^b^ 2. Audit of baseline data records 3. Audit of study developed activity directory and physiotherapy medical notes.	The reach of the delivery of the multi-faceted implementation strategy will be measured in two ways: (1) the Proportion of the different types of clinical physiotherapy teams across the district that participate in the implementation strategies; (2) the Number of new community physical activity providers identified and added into the study-specific activity directory.	1. Study recruitment log; 2. Audit of activity directory
Adoption	The percentage and representativeness of providers (clinical teams) that will adopt physical activity counselling, will be measured by (1) The number of clinical teams across the district who participated compared to the number invited to participate; (2) Percentage of eligible physiotherapists within clinical teams who participated in the study (participated in implementation strategies and attempted to deliver physical activity counselling to their patients).	1. Audit of study records kept by research team 2. Study-specific training and resources log	Number of physiotherapy clinicians or managers across the district that contribute content, resources or teaching within the multi-facted implementation strategy.	Study-specific training and resources log
Dose delivered	The dose of physical activity counselling will be measured across immediate and waitlist groups by physiotherapist self-reported proportion of time spent on physical activity counselling within total usual care sessions for recruited patient participants in the trial.	Study screening log and hospital occasion of service statistics^b^	Average dose (hours) per clinical team of implementation strategies delivered (education and training, audit and feedback, facilitation sessions, learning collaborative, tailored strategies for community referral).	Study-specific training and resources log
Fidelity (adherence)	The fidelity of physical activity counselling (elements included) delivered to patient-participants will be measured across immediate and waitlist groups in two ways, self-report and audit.	1. Physiotherapist self-report study checklist^b^ 2. Audit of EMR of all patient-participants^b^	Fidelity of multi-facted implementation strategy delivered will be measured by the percentage of implementation strategies that are implemented as prescribed in the study protocol including modes of delivery; COM-B domains, categories and intervention functions; proposed content and behaviour change techniques.	Study-specific checklist
Sustainability (maintenance)	The sustainability of physical activity counselling (elements included) will be measured in intervention clinical teams in a random sample of patients (5 per team) after the patient recruitment period.	Audit of EMR	Percentage of clinical physiotherapists from immediate implementation group involved in delivering implementation strategies or providing resources to waitlist implementation group.	Study-specific training and resources log

*EMR* Electronic medical record

^a^Primary implementation outcome; ^b^Data collected for immediate and waitlist groups and between-group difference calculated

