The co-primary effectiveness and implementation research questions are as follows:Do patients receiving physiotherapy care participate in greater amounts of planned physical activity at 6 months if their physiotherapist received the multi-faceted implementation strategy to support the implementation of brief physical activity counselling in routine care, compared to patients whose physiotherapist did not receive the multi-faceted implementation strategy (primary effectiveness outcome)?Do a greater proportion of patients receive brief physical activity counselling within routine physiotherapy care by physiotherapists who have received the multi-faceted implementation strategy compared to those who have not (reach, primary implementation outcome)?

Secondary research questions are as follows:Do patients receiving physiotherapy care participate in greater amounts of overall physical activity (self-reported, device-based [sub-sample]), report greater function and quality of life, fewer barriers to physical activity and better impressions of physiotherapy care at 6 months if their physiotherapist received the multi-faceted implementation strategy to support the implementation of brief physical activity counselling in routine care, compared to patients whose physiotherapist did not receive the multi-faceted implementation strategy?What is the adoption, reach, dose delivered, fidelity and sustainability of the delivery of brief physical activity counselling in routine physiotherapy care, and the delivery of the multi-faceted implementation strategy?What are physiotherapists’ experiences and reported barriers and facilitators to engage with the multi-faceted implementation strategy and delivering physical activity counselling within routine physiotherapy care?What is the cost-effectiveness of the multi-faceted implementation strategy and delivery of physical activity counselling in routine physiotherapy care?How successful are the targeted trial participation approaches for optimising participation of patients from Culturally and Linguistically Diverse (CALD) backgrounds in the trial, in terms of reach and retention?

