### Study sites and participant groups

This trial will be conducted across the South Western Sydney Local Health District (SWSLHD), a large health district within the state of New South Wales, Australia. This district includes lower socioeconomic areas, services almost one million people in both suburban and rural communities, 51% of households speak a language other than English at home and physical activity levels are 9% lower than the state average [35, 36]. The health district includes five public hospitals employing approximately 166 physiotherapists, and this study will recruit through physiotherapy departments at all five hospitals.

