#### Patient inclusion criteria

Patients will be recruited by the participating physiotherapists in each of the 30 clusters. Patient participants are likely to be affected by common and/or burdensome conditions such as, but not limited to, osteoarthritis, lower limb amputations, chronic pain, stroke, brain injury, cardiac and pulmonary disease. Patients will be eligible if they are at least 18 years old, are new patients of one of the participating physiotherapists during the recruitment period, live in the community (as opposed to residential care), able to leave their home without physical assistance from another person but may use a walking aid or wheelchair (anticipated within 6 months of recruitment), are without major cognitive impairment (e.g., diagnosis of dementia), do not have any medical reasons for which interventions aimed at increasing physical activity would be contra-indicated and have sufficient language capabilities to respond to written questionnaires in English, Arabic or Vietnamese.

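### Table 3's CALD reach measure describes who is in the sample and cannot by itself show how well eligible CALD patients were enrolled

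*Protocol article*

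**What the plan says.** The last secondary research question in the Background section reads "How successful are the targeted trial participation approaches for optimising participation of patients from Culturally and Linguistically Diverse (CALD) backgrounds in the trial", and it names reach and retention as the terms of success.

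The Reach row of Table 3 (Secondary implementation outcomes) opens with "Reach of the delivery of physical activity counselling will be measured in three ways". Item (1) is the primary implementation outcome. Its denominator is eligible new patients and its source is the study screening log. Item (2) is "Percentage of patient participants that are from culturally and linguistically diverse backgrounds", with the source given as "Audit of baseline data records". Item (3) is "Percentage of community physical activity providers referred to from number identified within the study". In the strategy-delivery column of the same row, one measure is "the Number of new community physical activity providers identified and added into the study-specific activity directory".

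Three other places bear on item (2):

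- Patient inclusion criteria: patients must "have sufficient language capabilities to respond to written questionnaires in English, Arabic or Vietnamese".
- Study sites and participant groups: the only population figure is that "51% of households speak a language other than English at home".
- Strategies to include CALD patient-participants: the targeted support is for Arabic and Vietnamese communities.

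**The concern.** Whether targeted recruitment reached a group depends on how many of those who could have joined did join. Item (2) has no such denominator. Its base is the enrolled sample, so it moves with the case mix of the 30 teams and with the language entry criterion as well as with enrolment success. A team serving a largely CALD caseload can post a high percentage while enrolling CALD patients poorly, and the reverse is equally possible.

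The measure also does not match its row label. It counts CALD participants in both arms whether or not they were counselled.

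At stake is the reach part of a stated research question. The article also presents testing ways to recruit and retain diverse patients as one of its contributions to the literature. Eligible patients who decline leave no baseline record, so their language may be hard to recover if it is not noted at screening.

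**Working it through.** The plan gives no expected value for item (2), so there is no figure to reproduce. The check is whether the percentage determines the relative enrolment of CALD patients.

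**Formula.** Let p be the CALD share of participants (what item (2) reports) and s the CALD share of eligible patients (not given). The ratio of CALD to non-CALD enrolment rates is

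ratio = [p / (1 − p)] × [(1 − s) / s].

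The ratio depends on s as much as on p.

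**Inputs.** 300 participants (Sample size section). Assumed for illustration: 120 of them CALD, so p = 0.40; 600 eligible patients; s from 0.25 to 0.65. The ratio does not depend on the 600. The value s = 0.51 borrows the district household figure, which is not a figure for eligible patients.

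| s | CALD enrolled / eligible | Non-CALD enrolled / eligible | Ratio |
|---|---|---|---|
| 0.25 | 120/150 = 80% | 180/450 = 40% | 2.0 |
| 0.40 | 120/240 = 50% | 180/360 = 50% | 1.0 |
| 0.51 | 120/306 = 39% | 180/294 = 61% | 0.64 |
| 0.65 | 120/390 = 31% | 180/210 = 86% | 0.36 |

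The same reported 40% fits CALD patients enrolling at twice the rate of others, or at about a third of it.

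**The same check from the other direction.** Take s = 0.51, with assumed consent of 40% among CALD and 60% among other patients:

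(0.51 × 0.40) / (0.51 × 0.40 + 0.49 × 0.60) = 0.204 / 0.498 = 41%.

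Equal consent in both groups where 41% of eligible patients are CALD also gives 41%. One number describes a clear shortfall and no shortfall at all.

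**Item (3), providers.** Assume 20 of 40 listed providers are referred to (50%) and 60 new ones are then added.

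| Share of new providers used | Providers used / listed | Percentage |
|---|---|---|
| 0% | 20/100 | 20% |
| 25% | 35/100 | 35% |
| 50% | 50/100 | 50% |
| 75% | 65/100 | 65% |

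The percentage falls only when new providers are used at a lower rate than those already listed. In the 25% row it drops from 50% to 35% while the number used rises from 20 to 35.

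**The case against.** The strongest reply is that the CALD share of participants is a direct description of diversity in the trial, that the 51% household figure offers a comparator, and that the article nowhere says item (2) is the only evidence for the question. The first and last parts stand: the percentage is worth reporting, and it is too strong to say the question cannot be answered. The comparator is weak. It counts households rather than eligible patients, covers languages beyond the two targeted, and takes no account of the language criterion. The article keeps screening spreadsheets for each team but does not say that language is recorded in them.

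A reader might infer three further faults that the document does not support.

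- **Retention goes unmeasured.** Table 3 covers counselling delivery and the implementation strategy, while the CALD approaches have their own section. Six-month surveys go to all participants, and language spoken at home is a pre-specified subgroup variable. Tabulating return by language is reporting detail.
- **Pooling all CALD backgrounds is an error.** The research question uses the same broad term, and a breakdown among participants needs no new data.
- **The provider percentage falls when the strategy succeeds in finding providers.** A fall is conditional, as the working shows. The percentage is a legitimate measure of directory uptake, and a drop caused by unused listings is informative.

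It is also fair to say that an eligible-patient denominator would not prove that the approaches worked, since there is no comparison group without them.

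**Conclusion.** The concern holds for item (2). The CALD percentage of enrolled participants cannot separate case mix from enrolment success, so by itself it does not answer the reach part of the question. In the illustration the same 40% is compatible with an enrolment ratio anywhere from 2.0 to 0.36. That range rests on assumed eligible shares of 25% to 65%, because the document gives none. The conclusion itself rests only on the definition of the measure and its data source.

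The weight is modest. Items (2) and (3) carry no between-group comparison and are to be presented descriptively. Neither co-primary outcome, the alpha nor the sample size depends on them. What makes the change worthwhile is that item (1), in the same table cell, already uses eligible patients from the screening log, so the better denominator is within reach. Item (3) does not need replacing.

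**What to change.** 1. Add a language field to the screening log already kept for the primary reach outcome.
2. Beside the existing percentage, report consented over eligible for Arabic, Vietnamese, other non-English and English speakers, with each group's difference from English speakers.
3. Report the number excluded by the language criterion separately. These patients are ineligible by definition and would otherwise drop out of the denominator unseen.
4. Tabulate 6-month survey return by the same groups, from data already collected.
5. Keep item (3) and, if wished, report beside it the number of distinct providers referred to, since the percentage can fall even as more providers are found and used.

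The cost is one extra entry per screened patient and a change to the Table 3 wording. The write-up should say that the results show differential enrolment and retention by language group, not a causal effect of the targeted approaches.

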### Implementation determinants

Implementation determinants will be evaluated using both quantitative and qualitative research methods. Patient-participant and physiotherapist factors (collected from demographic information) as well as contextual factors (hospital, team, patient environment) and trial characteristics will be considered in the determination of implementation success. Change in clinician self-reported capabilities, opportunities and motivations after receiving the multi-faceted implementation strategy will be evaluated using a survey with five-point Likert scales, with one being strongly disagree and five being strongly agree. This survey is based on the COM-B self-evaluation questionnaire [41] and adapted from Webb et al. [53] (see Supplemental file 2). The focus groups will be conducted with physiotherapists who participated in the implementation strategies at the end of the patient recruitment phase, led by LC and overseen by AH, SD and BB. Normalization Process Theory [54], the CFIR [42] and the Consolidated Criteria for Reporting Qualitative Research (COREQ) [55] will guide the conduct and reporting of this qualitative study. Figure 2 presents the logic model for how these determinants are hypothesised to influence the outcomes of the trial.

**Fig. 2 Fig2:**
[figure not shown]
Logic model for the BEHAVIOUR trial

### Strategies to include Culturally And Linguistically Diverse (CALD) patient-participants

Targeted approaches have been included within this study to include patients from Arabic and Vietnamese cultures, the two most prevalent CALD communities in South Western Sydney. Effectiveness outcome measures will be provided to the patient in their preferred language of English, Arabic or Vietnamese. Arabic and Vietnamese translations of the EQ5D-5L are available and have undergone testing of their psychometric properties [56, 57], and we received permission to use the following self-complete versions: Egypt, Arabic (version 1.1); Vietnam, Vietnamese (version 1.1) and Australian, English (version 1.1). The PROMIS-29 is available in English and Arabic, and we received permission to use the Arabic version. Within this project and led by BB, the PROMIS-29 was translated into Vietnamese using cross-cultural adaptations and forward and backward translation as per PROMIS-29 translation requirements. Following similar forward and backward translation processes, the IPEQ was also translated into Arabic and Vietnamese (processes to be reported in a separate publication). Finally, the other patient data collection forms were translated to Arabic and Vietnamese using a forward translation process and cross-checked by a team of multicultural health officers for accuracy.

To support the consent process, participant information sheets and consent forms have been translated into Arabic and Vietnamese. To further support informed consent, videos were developed in English, Arabic and Vietnamese by investigators BB and BS, in consultation with the SWSLHD Multicultural Health Service and consumer representatives from the Consumer and Community Participation Committee. The videos explain research concepts, reasons for participating in research and an overview of the study requirements in lay language, adapted for each target community. Access to these videos will be provided via a QR code attached to the participant information sheet on invitation to the study. To support the recruitment and retainment of CALD participants, the district Multicultural Health Service will provide support led by BS. Arabic and Vietnamese speaking multicultural health workers will provide telephone support at initial recruitment, assistance with the completion of survey questions at baseline and 6 months as required, and an additional check-in phone call at 3 months to support engagement with the project. These staff are blinded to physiotherapy team allocation.

### Data analysis and management

#### Sample size

The sample size calculation was undertaken in STATA 14.2 using the “clustersampsi” command. Recruitment of 300 patients undergoing physiotherapy is sufficient to detect a 1.5-h between-group difference in the self-reported time spent in planned physical activity per week, estimated at 3 h/week (SD 4.4 hours/week) (waitlist control group) to 4.5 h/week (immediate-implementation group) (a between-group difference found to be achievable in our previous study [58]). All calculations used 80% power, alpha = 0.025 (to account for co-primary outcomes), 15 clusters per arm, average cluster sizes of 10, baseline-covariance 0.6 and intracluster correlation 0.05. This sample size will also be sufficient to detect an absolute 25% difference in the proportion of eligible patients receiving brief physical activity counselling within routine physiotherapy care (primary implementation outcome (reach), 35% in the waitlist control group and 60% in the immediate-implementation group).

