#### Therapist inclusion criteria

A hospital clinical team that provides a service for inpatients or outpatients within SWSLHD and has one or more physiotherapists within the team will form each of the 30 clusters. The size of clinical teams is likely to be different across different areas of physiotherapy and hospitals. Examples of clinical teams likely to be recruited include musculoskeletal outpatients, inpatient rehabilitation and pulmonary rehabilitation. For the clinical team to be included in the trial there needs to be at least one physiotherapist within the team interested in participating and who meets the following eligibility criteria: they anticipate they will remain employed within SWSLHD for the next 12 months, are either permanent or on ≥ 6-month rotation in the identified clinical team, would treat ≥ 10 new eligible adult patients within their clinical team over a 3-month period and are not working in a split role across two clinical teams that have both been identified as potential clusters for the trial to avoid potential contamination.

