### Data collection methods and outcome measures

As a hybrid type II study [29], patient-level effectiveness and implementation outcomes will be measured. All effectiveness outcomes (excluding device-measured physical activity and impressions of physiotherapy) as well as demographic information and co-morbidities will be assessed at baseline to enable a description of the patient-participant’s baseline characteristics and to obtain values to enter as covariates in the models comparing groups at follow-up. At the time of consent, the treating physiotherapist will provide the participant with a copy of the paper-based survey. This will be completed independently by participants or assisted by study staff over the telephone who are blinded to physiotherapy team allocation. At 6 months post-baseline, follow-up paper-based surveys will be mailed to participants and followed up by blinded research staff if surveys are not returned by mail.

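### The 80% power for planned activity counts all 300 recruited patients as analysed, so it holds only if every 6-month survey comes back

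*Protocol article*

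**What the plan says.** The Sample size section claims that "Recruitment of 300 patients undergoing physiotherapy is sufficient to detect a 1.5-h between-group difference" in planned activity, taking the control group as "estimated at 3 h/week (SD 4.4 hours/week) (waitlist control group") and the immediate group as 4.5 h/week. It continues: "All calculations used 80% power, alpha = 0.025 (to account for co-primary outcomes), 15 clusters per arm, average cluster sizes of 10", with a baseline-covariance of 0.6 and an intracluster correlation of 0.05. The abstract confirms that 300 is a recruitment number: 30 teams, ten patients each on average.

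The outcome is the planned subscale of the IPEQ at 6 months. Under Data collection methods and outcome measures, "follow-up paper-based surveys will be mailed to participants and followed up by blinded research staff if surveys are not returned by mail". On clusters, Therapist inclusion criteria notes: "The size of clinical teams is likely to be different across different areas of physiotherapy and hospitals". The article states no loss rate, no inflation for loss and no coefficient of variation (CV) for the number of patients per team.

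**The concern.** A power calculation applies to patients who contribute an outcome. Here the number recruited and the number in the calculation are the same, 30 × 10 = 300, while the outcome is collected half a year later by a mailed questionnaire. If the inputs already need all 300, any non-return takes power below the stated value.

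Planned activity is one of two co-primary outcomes in a hybrid type II trial that gives effectiveness and implementation equal weight. A null effectiveness result would be read as coming from a trial with a 20% type II risk at 1.5 h/week, when the risk for the patients actually analysed would be higher.

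**Working it through.** **Inputs, all from Sample size.** Difference δ = 1.5 h/week; SD 4.4; 15 teams per arm; m = 10 per team; ICC 0.05; alpha 0.025; power 80%. Two readings are needed. Alpha is taken as two-sided, because the section does not say. The baseline-covariance of 0.6 is taken as the baseline-to-follow-up correlation, giving a variance factor of 1 − 0.6² = 0.64.

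**Reproducing the stated figure**

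- Design effect: 1 + (10 − 1) × 0.05 = 1.45.
- Patients with data per arm for 80%: 2 × (2.2414 + 0.8416)² × (4.4²/1.5²) × 0.64 × 1.45 = 151.8, or 304 in total after rounding up to 152 per arm.
- At 150 per arm: SE = 4.4 × √(0.64 × 1.45 × 2/150) = 0.489. Power = Φ(1.5/0.489 − 2.241) = 79.5%.

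This matches the stated 80% to rounding. Other readings do not: two-sided 0.05 (equivalent to one-sided 0.025) gives 86.5%, no baseline adjustment 58.3%, and a variance factor of 1 − 0.6 = 0.4 gives 94.9%.

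**Adding loss.** The rates are assumptions. With loss d, m = 10(1 − d), n per arm = 15m and design effect = 1 + (m − 1) × 0.05. The detectable difference is (2.2414 + 0.8416) × SE.

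| Assumed loss | n per arm | Design effect | SE (h) | Power for 1.5 h | Detectable at 80% (h/week) |
|---|---|---|---|---|---|
| 0% | 150 | 1.450 | 0.489 | 79.5% | 1.509 |
| 5% | 142.5 | 1.425 | 0.498 | 78.0% | 1.535 |
| 10% | 135 | 1.400 | 0.507 | 76.3% | 1.563 |
| 15% | 127.5 | 1.375 | 0.517 | 74.5% | 1.594 |
| 20% | 120 | 1.350 | 0.528 | 72.6% | 1.628 |
| 25% | 112.5 | 1.325 | 0.540 | 70.4% | 1.666 |

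The design effect falls a little as teams shrink, so power drops more slowly than the patient count.

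**Two further sensitivities, both on assumptions outside the article**

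- Unequal recruitment, design effect = 1 + ((1 + CV²)m − 1) × 0.05, with CV 0.4: power 77.1%, 74.0%, 72.3% and 70.3% at 0%, 10%, 15% and 20% loss.
- A noncentral t with 30 − 2 = 28 degrees of freedom, equal teams: 75.3%, 72.0%, 70.2% and 68.1% at the same losses.

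**Holm, as an option.** Reach at 35% v 60%, with 150 per arm and design effect 1.45, has pooled SE 0.0694 and unpooled SE 0.0672. Its power at 0.025 is Φ((0.25 − 2.2414 × 0.0694)/0.0672) = 92%. At 15% loss, planned activity has 74.5% power at 0.025 and 82.7% at 0.05. Treating the outcomes as independent, Holm gives 0.745 + 0.92 × (0.827 − 0.745) = 82%.

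**The case against.** **The arithmetic is sound.** This stands. 79.5% against 80%, or 304 against 300, is rounding. What fails is the claim that recruiting this number is enough, because the calculation needs that number analysed.

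**A condensed article may leave attrition to the full protocol.** This would answer a missing detail, but the figures published here leave no room for one. Under the only reading that matches the stated 80%, the inputs use every one of the 300 recruited.

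**Retention is supported.** Blinded staff chase unreturned surveys, and multicultural health workers offer telephone help and a 3-month call. This bears on how large the loss will be. It does not justify assuming none.

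**The shortfall is modest.** This is fair. At an assumed 15% loss the detectable difference moves from 1.5 to about 1.59 h/week, roughly 5 minutes. Type I error is untouched. Reach is recorded by physiotherapists on eligible new patients, so survey loss does not affect it.

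**Stronger readings that a reader might infer.** One is that any realistic loss leaves only 70–75% power. The documents do not support this: they give no loss rate, and 5–10% loss with equal teams leaves 78–76%. Reaching 70–75% takes about 14–26% loss, or an added assumption about CV or reference distribution. The article names GEE with exchangeable correlation but no t reference. Its remark on team size most naturally concerns staff, and each participating physiotherapist must expect at least 10 new eligible patients in 3 months. Some variation in recruits is implied by the word average, but its size is unknown.

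Another is that the 0.025 split is a mistake that throws power away. The split is valid. It appears only as a planning level, and the Quantitative analysis section fixes no test level or multiplicity rule, so Holm remains open.

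**Conclusion.** The claim that recruiting 300 suffices is wrong as written. The stated 80% is 79.5% with complete 6-month data and equal recruitment per team, and there is no reserve below that. For 300 recruited, power for 1.5 h/week is about 78%, 76%, 75% or 73% at an assumed 5%, 10%, 15% or 20% loss.

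These figures rest on two-sided alpha, on reading 0.6 as a correlation, on loss spread evenly over teams, and on the normal approximation. Unequal recruitment or a small-sample reference would take them lower by an amount the documents do not determine. The conclusion that no slack exists depends on none of the assumed loss rates.

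**What to change.** In Sample size, state that the 80% refers to 300 patients with 6-month data, and give power or detectable difference for 300 recruited over a stated range of loss. The sponsor should choose that range from its own experience of follow-up; the rates above are illustrations. Adding the assumed CV of recruits per team, the sidedness of alpha and the meaning of the 0.6 would make the calculation reproducible. The cost is a few sentences and a less favourable headline power.

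Two options go further. With equal teams, the normal approximation and alpha 0.025, recruiting about 12 per team (360) restores 80% at 15% loss, and about 13 per team (390) does so at 20%; this costs 60 or 90 more patients. Alternatively, specify Holm for the two co-primary outcomes: smaller p-value against 0.025, then the other against 0.05. It keeps familywise error at 5% and needs no extra patients. At 15% loss it lifts planned-activity power from about 75% to 82%, if the outcomes are independent and reach performs as assumed. Its drawback is that the interval level for the second outcome depends on the first result. It does not replace a stated allowance for loss.
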